# ASSESSMENT OF SAFETY

## Timing and methods for Assessing safety parameters

In the dose titration study, all adverse events will be registered in the separate adverse event eCRF section of the HIPEC registry (a section only used for trial purposes) as soon as possible after the event has occurred. The responsible investigator will need to alert the Sponsor and the DMC chairperson if a serious adverse event has occurred within 24 hours. A decision by the chairman of the DMC is issued whether to paus the trial for DMC review. Non-serious adverse events need not paus the trial accrual. Formal assessment by the DMC will be performed within 30 days after the last patients’ surgery on every dose level before moving to the next dose level.

In the subsequent efficacy study, registering the morbidity can be done within 4 weeks of discharge from the hospital. It will be registered in the HIPEC registry. Formal safety review by the DMC will only be performed during the interim safety evaluation, lest unexpected serious adverse events occur requiring an earlier review (all site investigators may initiate an earlier morbidity review).

In case of SAE (with at least a possible relationship to the study medication) or SUSAR, the sponsor will be responsible for informing via email all four participating HIPEC centers via their respective site investigator and site co-investigator that a SAE or SUSAR has been reported. An evaluation by the sponsor and the responsible site investigator will accompany the report. All DMC reviews will be released as well via email in the same manner

.

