## Definition, assessment and causality of adverse events

An AE is any untoward medical occurrence that does not necessarily have to have a causal relationship with the investigational product. An AE can be any unfavourable, unintended clinical sign, symptom, medical complaint or clinically relevant change in laboratory variables or clinical tests. Accidents, operations not pre-planned, changes in medication or deterioration in concurrent illness are also considered as AEs.

The Investigator should rate the intensity of any AE as follows:

*Mild:* Defined as Clavien-Dindo grade I and II.

*Moderate:* Defined as Clavien-Dindo grade 3a.

*Severe:* Defined as Clavien-Dindo grade 3b-5.

The Investigator shall judge whether or not, in his/her opinion, the AE is associated with the study treatment. When stating the causality, the following nomenclature should be used:

*Unrelated:* There is little or no chance that the study treatment caused the AE.

*Possibly related:* The association of the AE with the study treatment is unknown, however, the AE is not clearly due to another condition.

*Probably related:* A reasonable temporal association exists between the AE and the study treatment. Based on the Investigator’s clinical experience, the association of the AE with the study treatment seems likely.

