## Safety parameters

Clavien-Dindo morbidity was chosen as the most relevant morbidity grading system. The oxaliplatin/irinotecan/5-FU combination for systemic chemotherapy is already well known in oncology under different acronyms (FOLFIRINOX, FOLFOXIRI). As such, the toxicity profile of this triple combination is already known. This study will assess whether it is compatible with a surgical intervention using the Clavien-Dindo surgical classification. However, some basic blood chemistry as specified in section 8.3 (extended part of the HIPEC registry employed only for the dose titration study) will be added to verify the rate of non-surgical toxicity. As the 24-hour EPIC has not previously been dose-titrated, we will titrate to a maximum of 850 mg/m^2^. Clavien-Dindo 3a was excluded as a stopping factor due to its common use postoperatively after CRS+HIPEC for draining fluid collections (most commonly pleural effusion often caused by diaphragmatic stripping of the peritoneum and is dependent upon the extent of the stripping).

All patients will be reviewed at each of the dose levels by the DMC prior to advancing to the next level. It is Clavien-Dindo grade 3b-5 morbidity that will be reviewed. A dose level with ≤1/3 or ≤2/6 with 3b-4b morbidity may proceed to the next dose level. Max tolerated 3b-4b morbidity is 33 %. Statistical testing is unnecessary. All grade 5, leading to death, will halt study progression. A formal review with the DMC will ensue before the study will be allowed to continue or be terminated permanently. Two grade 5 events may be cause for study termination after DMC review.

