### Interim safety analysis of the Efficacy study

After randomization, the Clavien-Dindo grade 3a-4b morbidity is expected to be approximately 25-35% when treating patients with the dose of 5-FU determined from the dose titration study. During the interim analysis of the efficacy part of the trial, the DMC will use the morbidity rate of the standard arm and compare it to the experimental arm. If all Clavien-Dindo grade 3-4 complications resolve in-hospital and occur at a maximum rate of 40%, the trial will pass the interim review. If complications lead to permanent sequelae or the rate is higher than 40% a detailed review by the safety committee will ensue prior to letting the efficacy study continue. Comparison with the standard arm will assist in determining the risk/possible benefit ratio. In particular, if the mortality rate is increased, it will be grounds for discontinuing the trial. The trial may be allowed to continue despite increased morbidity if the mortality rates are the same and if the morbidity is of a temporary nature, not leading to permanent functional loss. The decision will be made by the DMC. If necessary, dose reduction may be considered in order to continue and complete the efficacy study.

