## Reporting of adverse events, serious adverse events, AND suspected unexpected serious adverse reactions

All adverse events will be reported in a separate eCRF adverse event report section of the HIPEC registry created for this trial. It is the responsibility of the site investigator or co-investigator to fill out an eCRF Adverse Event form in the HIPEC registry. All investigators have access through their SITHS ID cards to the registry. One form per AE is to be filled out. It may be filled out as part of the postop follow-up at predetermined time points of follow-up, but it may be filled out in between these time points since the patients are admitted to the hospital and under daily surveillance during 10-14 days. If classified as SAE it needs to be filled out within 24 hrs from being informed about the event.

Serious adverse events with a possible or probable relationship to the study medication including events leading to a deadly outcome need to be brought to the attention of the DMC. The adverse event eCRF section of the HIPEC registry will include a list box if an adverse event needs to be brought to the DMC for review. An automated email will be sent to the coordinating investigator (who is also the sponsor representative) who will be responsible for discussing the event with the DMC.

The Investigator’s initial report of serious AEs should as far as possible be supplemented by detailed information on diagnosis/symptoms, the relationship with the start of treatment and any further relevant data in the eCRF section.

If the SAE is assessed as unexpected and possibly/probably related to the IMP, i.e. a Suspected, Unexpected Serious Adverse Reaction (SUSAR) that are fatal or life-threatening, it shall be reported to the Medical Products Agency (MPA) as soon as possible and at the latest within 7 calendar days from the first knowledge by the Sponsor. The report shall as far as possible be supplemented by additional information, but at the latest within a further 8 calendar days. It is the responsibility of the Sponsor to report SUSARs to the MPA. It will be reported on CIOMS forms by e-mail to be registered in the EudraVigilance database by MPA.

The reporting of other SUSARs to the MPA shall be done as soon as possible, but not later than 15 calendar days after the first knowledge by the sponsor.

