#### Interim analysis

The Clavien-Dindo grade 3-4 morbidity is expected to be approximately 0.35 (35%) for patients receiving the maximum dose of 5-FU. Allowing for a small increase in morbidity to 0.40 and an accepted 95% confidence interval width of 0.15, at least 66 patients are needed in the experimental arm to determine whether the arm deviates from the expected morbidity rate. The total sample size will be 140 (70 per arm) for an interim trial safety evaluation (circa 50% of trial included). If the Clavien-Dindo grade 3-4 morbidity falls outside of the 40% mark, then a Fisher’s exact test comparison between the standard and experimental arm will be performed together with a mortality comparison. Concerning in-hospital mortality, a maximum rate of 5% will be set. This planned interim safety evaluation will be unpublished. If the morbidity is increased beyond the set mortality limit or the increase is of a more serious nature, the trial will either be discontinued or alternatively, depending on the character of the complications, a lower dose level may be employed.

The overall survival and recurrence free survival will be reviewed during this interim safety evaluation to see if a primary endpoint of overall survival is attainable with increased cohort size instead of 12-month RFS. If attainable depending on inclusion rate, the endpoint will be changed, and a new sample size calculation will be performed. Likewise, a choice between 3 or 5 year follow-up will be made. Alternatively, trial futility will be determined if no differences at all are forthcoming even in the RFS setting. In this case, the trial will close prematurely. A decision to close the trial is made by the sponsor in conjunction with site investigators.

Possible changes of dose level, endpoint, sample size calculation or other substantial changes will be submitted to the MPA and ERA as an amendment to the protocol.

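### Phase III has no stated rule that brings every in-hospital death to the DMC, or that convenes it once the 5% mortality limit is certain to be exceeded before the 140-patient interim

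*Protocol*

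**What the plan says.** **When the DMC meets.** Section 12.1 of the Protocol says of the efficacy study: "Formal safety review by the DMC will only be performed during the interim safety evaluation, lest unexpected serious adverse events occur requiring an earlier review". It adds that any site investigator may start an earlier morbidity review. Section 13.2.1 places the interim at 140 patients, 70 per arm, out of 326.

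**What must reach the DMC between reviews.** Section 12.6 defines what is passed on for the committee's notice: "Serious adverse events with a possible or probable relationship to the study medication including events leading to a deadly outcome need to be brought". The adverse event form "will include a list box if an adverse event needs to be brought to the DMC for review". An automated e-mail then goes to the coordinating investigator, who is also the sponsor representative and who takes the event to the DMC. Under section 12.2 the investigator decides relatedness, and an event is unrelated when "There is little or no chance that the study treatment caused the AE". Section 10.5 says that treatment is not blinded.

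**What the DMC judges at the interim.** Section 13.2.1: "Concerning in-hospital mortality, a maximum rate of 5% will be set". Section 12.5.1 adds a criterion without a number: "In particular, if the mortality rate is increased, it will be grounds for discontinuing the trial".

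**What applies in phase I.** For dose titration, section 12.1 has no causality condition: "The responsible investigator will need to alert the Sponsor and the DMC chairperson if a serious adverse event has occurred within 24 hours". Section 8.2.1 pauses inclusion for any grade 5 event. Section 12.5, in a paragraph about dose levels, says "All grade 5, leading to death, will halt study progression", followed by formal DMC review.

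**The concern.** The mortality limit and the reporting rule do not count the same deaths. The limit covers in-hospital deaths from any cause. The reporting rule, read literally, covers only those that an unblinded investigator links to treatment. A death judged unrelated counts toward the 5% at the interim but need not reach the DMC before then.

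Nor does any count of deaths oblige the DMC to meet. The experimental arm could already be certain to exceed the protocol's own limit while patients are still being randomized to it. This matters more here than in a usual phase III trial. Section 13 of the background (justification of study design) is explicit that the interim takes the place of a phase II trial, and section 16.2 says that the intensified arm has not been followed prospectively in a systematic way.

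**Working it through.** **Inputs from the Protocol.** Limit 5% and interim at 70 per arm (13.2.1). Planned recruitment 100 per year, so 50 per arm per year (20.5). The 5% is a set value, so there is no derived figure to reproduce.

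**Inputs that are assumptions.** True in-hospital mortality *p*: the documents give no expected rate, so a range of 2% to 8% is used. Share *u* of in-hospital deaths judged unrelated: 10% or 25%. The limit is read per arm unless stated otherwise.

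**Step 1: how many deaths breach the limit.**
- Per arm: 3/70 = 4.3% and 4/70 = 5.7%, so 4 deaths breach it. Because 3/60 = 5.0% and 4/79 = 5.06%, four is the first count above 5% for any arm size from 60 to 79. A modest imbalance at the interim changes nothing.
- Pooled: 7/140 = 5.0% and 8/140 = 5.7%, so 8 deaths are needed.

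**Step 2: chance that the 4th experimental-arm death comes by patient 70.** With X ~ Binomial(70, *p*), this is P(X ≥ 4).

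**Step 3: chance that the limit is breached but the DMC has been sent fewer than 4 deaths.** On the literal reading of section 12.6, each death is sent with probability 1 − *u*. The chance is the sum over x ≥ 4 of P(X = x) × P(Binomial(x, 1 − *u*) ≤ 3).

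| Assumed true mortality | P(X ≥ 4 of 70) | ≥4 occurred, <4 sent, u = 10% | ≥4 occurred, <4 sent, u = 25% |
| --- | --- | --- | --- |
| 2% | 5% | 1% | 3% |
| 3% | 16% | 4% | 9% |
| 5% | 47% | 8% | 20% |
| 8% | 82% | 7% | 21% |

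**Step 4: how early the certainty arrives.** The patient number of the 4th death is negative binomial. At 8%, given that it comes by patient 70, its mean is 41.4. That is 70 − 41.4 = 28.6 experimental-arm patients before the interim, or 28.6/50 × 12 = 6.9 months. This figure needs a mortality above the protocol's own limit.

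**Step 5: the two phases side by side.** In phase I, section 12.1 sends every SAE to the DMC chairperson and section 8.2.1 pauses inclusion at any death. In phase III, section 12.6 attaches relatedness to what must be sent, and no section states a count or running rate at which the DMC meets.

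**The case against.** **Section 12.6 may already cover all deaths.** Its phrase about fatal events can be read as adding every death. Grammatically it more naturally describes a subset of related SAEs. On the wider reading the column for reporting loss in the table falls to zero and the reporting part of the fix is only a clarification. There would still be no count that convenes the DMC.

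**Section 12.5 may halt the trial at any death.** The sentence is not expressly limited to phase I. Its paragraph concerns dose levels, and section 8.2.1 has the matching titration rule, so phase I is the likelier reading. If it did cover phase III, it would sit badly with section 12.1.

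**There are other safeguards.** Section 12.1 has the sponsor e-mail SAEs with at least a possible relationship, and SUSARs, to site investigators at all four centers, and any of them may call a review. Unrelated is a demanding category, so many early deaths would be sent. These points stand and make the gap smaller. The investigators' route is discretionary, has no threshold, and the e-mails carry the same causality condition. The annual safety report (12.8) and the sponsor's right to stop (20.4) do not convene the DMC.

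**The DMC charter may contain the trigger.** Section 12.4 leaves the committee's working rules to it, and it is not shown. This stands: the finding is about what the protocol states.

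**The 5% is an interim criterion and names no arm.** Correct. The four-death count holds only per arm, and a breach leads to DMC judgement rather than automatic stopping.

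**Tighter reporting in phase I is normal.** Agreed; the difference between phases is not an error in itself. The problem is the mismatch with an all-cause limit.

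A reader might infer that phase III deaths go unmonitored, or that the experimental arm is likely to breach the limit. The documents support neither. Related SAEs go to the DMC case by case, and the protocol reports no mortality increase from adding EPIC (5.4, 16.2, 16.3).

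**Conclusion.** The point holds as a cheap safety improvement, not as a failure of oversight. The protocol schedules one formal phase III review, gives no threshold for an earlier one, and on its literal wording filters by investigator-judged causality the deaths that count toward an all-cause limit. It does not say whether that limit is per arm or pooled.

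The size depends on unknown mortality. At 2% to 3%, a 4th experimental-arm death by patient 70 is uncommon (5% to 16%), and the chance that the causality condition keeps the DMC below the true count at a breach is about 1% to 9%. At 5% to 8%, the corresponding figures are 47% to 82% and about 7% to 21%. The last range in each case rests on two assumptions together, the true mortality and 10% to 25% of deaths judged unrelated, and on the literal reading of section 12.6. Confidence is medium because of the two ambiguous sentences and the unseen charter.

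**What to change.** 1. **Sections 12.1 and 12.6:** state that in phase III every in-hospital death is reported to the DMC with its treatment arm, whatever its judged causality or expectedness.
2. **Section 13.2.1:** state that the 5% in-hospital mortality limit applies to the experimental arm.
3. **Protocol or DMC charter:** state that the DMC is convened at the 4th in-hospital death among the first 70 experimental-arm patients, with standard-arm counts shown alongside and the outcome at its discretion.
4. **Section 12.5:** say whether the grade 5 halt applies to dose titration only or to phase III as well.

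The cost is a few sentences. Site work hardly changes, since SAE forms are already due within 24 hours (12.6). The trigger calls a review and stops nothing. The downside is an unscheduled DMC meeting when mortality is in fact acceptable: probability 5% or 16% at a true rate of 2% or 3%, and 47% at exactly 5%.

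### Protocol section 12.1 releases all DMC reviews to site investigators, with no exception for the phase III interim review and no limit on content, so by-arm interim results can reach the treating physicians

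*Protocol*

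**What the plan says.** Section 12.1 (Timing and methods for assessing safety parameters) makes the sponsor responsible for "informing via email all four participating HIPEC centers via their respective site investigator and site co-investigator" of related SAEs and of SUSARs. It then adds: "All DMC reviews will be released as well via email in the same manner". The sentence does not separate phase I from phase III, or a recommendation from the data behind it.

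The same section identifies the phase III review that the rule covers: "Formal safety review by the DMC will only be performed during the interim safety evaluation", unless unexpected serious events prompt an earlier one, which any site investigator may initiate.

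The content of that review is given in two places:

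- Section 12.5.1: "the DMC will use the morbidity rate of the standard arm and compare it to the experimental arm".
- Section 13.2.1, Interim analysis: if morbidity falls outside the 40% mark, a Fisher's exact test between arms and a mortality comparison follow. In addition, "The overall survival and recurrence free survival will be reviewed during this interim safety evaluation", partly to see whether overall survival could become the primary endpoint. On futility, "trial futility will be determined if no differences at all are forthcoming even in the RFS setting", and "A decision to close the trial is made by the sponsor in conjunction with site investigators". On confidentiality it says only: "This planned interim safety evaluation will be unpublished".

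Section 12.4 refers to a DMC charter, which is not among the documents at hand.

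**The concern.** Interim comparisons are normally kept from those who enrol and treat, because the knowledge can alter how the rest of the trial is run. Here the recipients named in section 12.1 are the treating physicians. The section on the role of treating physicians says that the investigators and co-investigators are nearly all those who give HIPEC in Sweden.

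The trial is open label (section 10.5), and these physicians keep discretion after allocation in three places that bear on RFS:

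- the optional 25% reduction of chemotherapy dose (section 10.1);
- adjuvant chemotherapy, which follows each center's routine (section 10.6);
- the timing of any CT outside the schedule, since recurrence is dated by the scan that finds it and a scan before 12 months counts (sections 11 and 11.1.1).

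If knowledge of the interim result shifts any of these differently in the two arms, the RFS comparison is biased, and the direction cannot be known in advance. The same knowledge can change who is offered the trial, which affects accrual and case mix.

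**Working it through.** **1. Does the release rule cover the phase III interim review?** Yes. The rule in section 12.1 applies to all DMC reviews. The same section names the interim safety evaluation as the planned formal DMC review in phase III, and section 12.4 gives the DMC the decision to continue after it. No exception is stated.

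**2. What could be released?** Two routes have to be kept apart.

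| Information | Route to site investigators |
| --- | --- |
| Morbidity by arm, and mortality by arm if the 40% mark is passed | Part of the DMC review (12.5.1, 13.2.1), released under 12.1 |
| OS and RFS by arm | Looked at in the same evaluation (13.2.1), where the DMC is not named as the reader. The futility criterion is the absence of a difference, and site investigators share the closure decision, so they would need the comparison whatever 12.1 says |

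**3. The plan's own sample size.** Inputs from section 13.3: 50% against 66%, alpha 5% (two-sided assumed), 80% power. With the pooled formula and mean rate 0.58:

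n = [1.96 × √(2 × 0.58 × 0.42) + 0.842 × √(0.50 × 0.50 + 0.66 × 0.34)]² / 0.16² = (1.368 + 0.580)² / 0.0256 ≈ 148.2 per arm.

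The plan's 148 is reproduced (149 if rounded up). Then 148 × 1.10 ≈ 163 per arm, or 326 in total.

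**4. Patients still to be randomised.** The interim takes place at 140 patients (section 13.2.1). 326 − 140 = 186, and 186/326 = 57%. This is an upper limit: morbidity may be entered up to four weeks after discharge and no accrual pause is stated. At 100 patients per year, each month between the 140th patient and the email removes about 100/12 ≈ 8.

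**5. Patients without 12 months of follow-up.** At 100 per year (section 20.5), with uniform accrual, the 140th patient enters at 140/100 = 1.4 years. Those with at least 12 months of follow-up number 100 × (1.4 − 1.0) = 40. So 326 − 40 = 286, and 286/326 = 88%. This is also an upper limit on outcomes still open, because some of the 100 patients entered in the last year will already have recurred. With constant hazards matching 50% and 66% at 12 months:

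- control: hazard −ln 0.50 = 0.693; average proportion with an event 1 − 0.50/0.693 = 0.279;
- experimental: hazard −ln 0.66 = 0.416; average proportion 1 − 0.34/0.416 = 0.182.

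The mean is about 0.23, or 23 patients. 286 − 23 = 263, and 263/326 = 81%.

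**6. How reliable would the circulated RFS comparison be?** Even with 12-month data on all 70 per arm, power for 50% against 66% is Φ[(0.16 × √70 − 1.368)/0.689] = Φ(−0.04) ≈ 48%. With the roughly 20 per arm who have 12 months of follow-up, it is Φ[(0.16 × √20 − 1.368)/0.689] = Φ(−0.95) ≈ 17%. The figures could influence conduct while saying little about the true effect.

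**The case against.** The strongest reply is that section 12.1 does not define a released review. It might mean the committee's conclusion only, and the charter may say so. That stands as a limit: by-arm tables in the email are a strong inference from sections 12.5.1 and 13.2.1, not a stated instruction. But a charter that limited release would sit badly with a protocol sentence that covers all reviews, so the sentence needs correcting either way.

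Four stronger readings are tempting, and the documents do not support them.

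- **That 12.1 contradicts 13.2.1.** A reader might infer this from "This planned interim safety evaluation will be unpublished". That wording limits publication. Emailing investigators is not publishing, so the two sections are compatible.
- **That patients randomised before and after the email are not comparable, so the result is biased.** Randomisation still balances the arms within each period. A change in who is enrolled alters case mix in both arms and may slow accrual. Bias needs conduct that differs by arm after allocation.
- **That scan assessment is compromised.** Radiologists read the CTs without knowing the allocation (section 10.5) and are not named recipients. The 12-month CT is mandatory and routine CTs are six-monthly (section 11.1.1). Only the timing of additional scans is exposed.
- **That 12.1 alone leaks RFS.** Section 13.2.1 brings OS and RFS to site investigators by its own closure clause. If that were repaired, 12.1 would clearly still release morbidity and mortality, but RFS only if the DMC's review contains it.

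It is also fair to say that open-label investigators already see their own center's outcomes by arm. The email would add the pooled comparison, which no single center has.

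**Conclusion.** The point holds as a weakness in how interim information is controlled. Section 12.1 has no exception for phase III and no limit on content, and section 13.2.1 puts site investigators into a decision that turns on between-arm results. By-arm interim findings can therefore reach the treating physicians with up to 186 patients (57%) still to be randomised and at most about 286 (88%) short of 12 months' follow-up. About 263 (81%) would have outcomes still open under the constant-hazard assumption.

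The 286 and 263 assume uniform accrual at 100 per year; faster accrual would raise them and slower accrual would lower them. For the 100 patients enrolled in the year before the review, selection and intraoperative dosing are already done, so only later management can be affected. No size or direction of bias can be derived from the protocol. This is an inexpensive improvement, not a demonstrated bias, and it should be made before the interim review because a disclosure cannot be withdrawn.

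**What to change.** Replace the release sentence in section 12.1 with text such as:

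> After each phase III DMC review, sites receive only the committee's recommendation (continue, continue with modification, pause or stop) and any safety information needed for patient care. Tables by arm and all OS and RFS results stay within the DMC until the primary analysis.

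Phase I dose-level reviews may still be circulated, since there is no randomised comparison to protect.

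Changing 12.1 alone is not enough. It would collide with section 13.2.1, where the sponsor and site investigators decide on closure from RFS differences and the endpoint may be changed after a look at OS and RFS. Amend section 13.2.1, and section 13.5 with it, so that decisions on futility, closure and change of endpoint rest on a DMC recommendation and not on by-arm OS or RFS shown to the sponsor and site investigators. Mirror this in the DMC charter.

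The cost is a short amendment to three sections and the charter, and less interim detail for the sponsor and investigators. SAE and SUSAR notification and the sample size are unchanged.
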